### Participants

This study will be conducted in the population with a proximal humerus fracture treated conservatively at the Centre intégré universitaire de santé et de services sociaux de l’Estrie - Centre hospitalier universitaire de Sherbrooke (CIUSSS de l’Estrie CHUS). To be included, participants will have to: 1) return home after discharge from hospital or emergency; 2) be apt to do exercises; 3) have a sufficient verbal and written comprehension to participate to the treatment and evaluations; 4) have access to high speed internet connection at home. Participants with the following characteristics will be excluded from the study: 1) intra-articular proximal humerus fracture types (often susceptible to longer rehabilitation periods and a higher risk of complications); 2) presence of any other upper-limb fracture that can interfere with rehabilitation; and 3) surgical treatment following the fracture.

A sample of 52 participants with a proximal humerus fracture and responding to the eligibility criteria will be included. Participants will be screened by the orthopaedic research team through the orthopaedic resident or nurse who proceeds to the installation of the removable splint. At that time, the research team will briefly inform the patient on the study and will obtain his/her authorisation to be contacted by phone by a member of the teletreatment research for a more detailed evaluation of eligibility and explanation of the study. Following this telephone interview, if the participant is still interested and meets all the eligibility criteria, an appointment will be scheduled to obtain the informed consent (approved by local ethic committee; CIUSSS de l’Estrie - CHUS, and perform the first evaluation (T1). Immediatly following visit T1, each patient will be randomised to either the TELE or the CLINIC group. The randomised list has been generated electronically using block randomization of size 4. The evaluator is the only one who will be blind to the randomisation.

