#### Shoulder functional measures

Shoulder global function will be measured with the Constant score [36], which is the primary outcome measure. This questionnaire allows the assessment of four outcomes related to shoulder function: 1) pain; 2) activities of daily living (sleeping, work, leisure); 3) range of motion; and 4) muscle strength. The total is on 100 and a higher score indicates a higher shoulder function. According to a systematic review of the psychometric properties of the Constant score, the reliability of this questionnaire is excellent (ICC, 0.89; 95 % confidence interval, 0.79–0.94) [37], and the internal consistency, evaluated with the Cronbach alpha, ranges from 0.60 to 0.75 suggesting that it measures different aspects of function [38, 39].

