### Statistical methods

The principal analyses intend to test the noninferiority of the TELE intervention versus the CLINIC intervention. We aim to recruit a total of 52 participants, or 26 participants per group. Sample size was determined with data from a previous study on the Constant score [44], which is considered in this study as the primary outcome measure. With 26 participants per group, within the context of a unilateral t-test with an alpha level set at 0.05, the power of the study to reject non-equivalence hypothesis would be at 69 % for a difference of 10.3 or less (standard deviation = 17). This noninferiority point is under the minimal clinically important difference of 10.4 points on the Constant score [44].

Participant characteristics in each group will be described pre-intervention (T1) using mean and standard deviation (continuous variables) or proportion (categorical variables). Groups at baseline will then be compared using *t*-test or chi-squared test.

First, the data will be analysed according to the received intervention (per protocol), and then, according to the assigned group (intention to treat analysis). A sensitivity analysis will be used to explore the effect of compliance or screen failures: missing data will be replaced by extreme data (no change following intervention or most favorable change noted in the study). Any non-robustness of the revealed results by comparison of strategies will be noted.

Economic analysis is of cost-efficacy type. Cost by change-unit of the principal dependant variable (Constant score) will be determined for both groups. Differential cost will then be established.

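### The missing-data sensitivity analysis gives its extreme values no direction by arm, so it need not test the case that threatens noninferiority, and it names screen failures, who are never randomised

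*Protocol article*

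**What the plan says.** The trial's main question is noninferiority: "The principal analyses intend to test the noninferiority of the TELE intervention versus the CLINIC intervention". The outcome is a 100-point scale on which higher is better: "Shoulder global function will be measured with the Constant score [36], which is the primary outcome measure". The Statistical methods section plans a per-protocol analysis, then an intention-to-treat analysis, and then a further check: "A sensitivity analysis will be used to explore the effect of compliance or screen failures". The rule for that check is that "missing data will be replaced by extreme data (no change following intervention or most favorable change noted in the study". The section adds that results which differ between strategies will be noted. It does not assign either extreme to an arm.

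The Participants section settles eligibility by telephone before the consent and T1 appointment, and then states: "Immediatly following visit T1, each patient will be randomised to either the TELE or the CLINIC group".

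**The concern.** In a superiority trial, giving missing patients in both arms the same value is usually cautious, because it pulls the arms together. In a noninferiority trial, pulling the arms together moves the estimate towards the conclusion that the trial hopes to reach. The check that matters is one in which TELE patients who drop out have done worse than assumed. The stated rule does not require that check, and on its plain reading does not perform it. A reader could then take agreement between the analyses as evidence of robustness although the unfavourable direction was never tried.

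The stated target is also wrong. Screen failures leave before randomisation, so they have no assigned arm and no T2 score to replace. The patients who matter are those randomised without a T2 measurement.

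**Working it through.** **Inputs from the article (Statistical methods).** Size: "We aim to recruit a total of 52 participants, or 26 participants per group". Test: "within the context of a unilateral t-test with an alpha level set at 0.05". Power, margin and SD: "the power of the study to reject non-equivalence hypothesis would be at 69 % for a difference of 10.3 or less (standard deviation = 17".

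**Assumptions.** The article gives neither a missing-data rate nor a mean change. I take 10-20% missing (or 2 or 5 of 26 per arm), a mean CLINIC change of 15 to 40 points with 30 as the reference, SD 17 for the change, and missingness unrelated to outcome.

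**Step 1: the plan's own figure.** Standard error = 17 × √(2/26) = 4.715. Noncentrality = 10.3 / 4.715 = 2.185. The noncentral t with 50 degrees of freedom at one-sided 0.05 gives 69.5% power, which reproduces the stated 69%.

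**Step 2: same value c in both arms.** With missing shares pT and pC, the filled-in difference is

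(1 − pT)·μT − (1 − pC)·μC + (pT − pC)·c.

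If pT = pC = p, the last term vanishes and the difference is (1 − p) times the true one, whatever c is. With a true difference of -10.3:
- 10% missing: 0.90 × -10.3 = -9.3
- 20% missing: 0.80 × -10.3 = -8.2
- 5/26 missing: (21/26) × -10.3 = -8.3

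If the shares differ, the term in c decides the direction. Take μC = 30, μT = 19.7, 20% missing in TELE and 10% in CLINIC. *No change* (c = 0) gives 0.8 × 19.7 − 0.9 × 30 = -11.2, which is worse for TELE. *Most favourable* gives about -4.8 by simulation, which is better for TELE.

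**Step 3: false noninferiority when TELE is truly worse by the full margin.** 40,000 simulated trials per scenario, 26 per arm, pooled one-sided t-test at 0.05 against -10.3. A complete-case analysis gives 5%.

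CLINIC change 30, each patient independently missing, so that counts differ between arms by chance (repeat runs agree within about half a point):

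| Missing per arm | *No change* in both arms | *Most favourable* in both arms |
|---|---|---|
| 10% | 7.5% | 7.0% |
| 15% | 9.0% | 8.4% |
| 20% | 10.3% | 9.9% |

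Exactly equal missing counts in the two arms:

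| CLINIC change | *No change*, 2/26 | *No change*, 5/26 |
|---|---|---|
| 15 | 6.9% | 11.0% |
| 20 | 6.3% | 9.7% |
| 30 | 5.3% | 6.6% |
| 40 | 4.0% | 3.9% |

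Under equal counts, *most favourable* gives 3.8-5.0% throughout, because the constant raises the pooled SD from 17 to about 20-23 and offsets the shrinkage. Much of the excess in the first table therefore comes from chance imbalance in the missing counts, not from shrinkage alone.

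With 20% missing in TELE and 10% in CLINIC (CLINIC change 30), *most favourable* gives 23% and the companion *no change* analysis about 3%.

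**Step 4: all strategies required to agree.** With the same value in both arms and CLINIC change 30, complete-case, *no change* and *most favourable* all wrongly declare noninferiority in 2.1%, 2.1% and 2.0% of trials at 10%, 15% and 20% missing. With 20% versus 10% missing the figure is 1.9%. Over the assumptions tried it stays between about 1% and 5%.

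**Step 5: crossed extremes, 5 of 26 missing per arm, CLINIC change 15 to 40.**
- TELE *no change*, CLINIC *most favourable*: false noninferiority 0.1% or less.
- TELE *most favourable*, CLINIC *no change*: 67-89%.

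The first crossing is also severe when the arms are truly equal. For CLINIC changes of 20 to 40, power falls to 15-29% with 2/26 missing and to 0-1.4% with 5/26.

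**Step 6: screen failures.** The Participants section puts eligibility, consent and T1 before randomisation. The Statistical methods section imputes a change after the intervention. A screen failure has neither an arm nor such a change, so the two sections cannot both apply.

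**The case against.** Four points are fair.

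- The article never says that both arms receive the same value. A best/worst crossing fits the same words, and a full analysis plan may settle the assignment. This stands: the same-value reading is the plain one, not a stated one. But the article does fix a rule, and a rule open to both crossings has no determined result.
- The extremes are compared with the main analyses and do not replace them. A reader might infer that the plan inflates the trial's type I error. The article does not support that. The main test is untouched, and joint agreement is rarer than a false positive in the complete-case test. That protection does assume that the complete-case analysis itself holds 5%, which is the assumption that a sensitivity analysis is meant to question.
- A reader might take 23% as the size of the problem. It is one extreme under one dropout pattern. Its companion gives about 3%, and that disagreement is what the plan says it will note. Nor is inflation general: it is small or absent with exactly equal missing counts, except under *no change* with a modest mean change.
- The term screen failures may be loose wording for dropouts. Probably so, but as written it points to the wrong people.

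**Conclusion.** The concern holds in a limited form. The screen-failure wording is wrong on the article's own account of recruitment, and this rests on no assumption. The extreme-value rule is badly suited to a noninferiority question, because it does not require a scenario adverse to TELE. On the same-value reading with equal missingness it moves the estimate towards zero by about the missing share, and any adverse push then comes only from unequal dropout. On the crossed reading its result is undetermined, from about 0% to 67-89% false noninferiority at 5/26 missing.

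The 7-10% rates for a single extreme depend on assumed missing rates, an assumed mean change and random missing counts. They describe one analysis read alone, not the trial's error rate. What is at stake is the value of the robustness check. It should be corrected, but the primary result does not hang on it.

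**What to change.** 1. Replace the reference to screen failures with randomised participants without a T2 measurement.
2. Replace the extreme-value rule with one directed against noninferiority: multiple imputation of missing T2 Constant scores within each arm from T1 values, followed by a tipping-point analysis that lowers only the imputed TELE values until noninferiority is lost. Report that reduction so that readers can judge whether it is plausible.
3. If an extreme case is kept, state its direction in advance (TELE missing = no change, CLINIC missing = most favourable change) and label it a worst-case bound.

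The cost is a few sentences and a few hours of analysis, with no new data. The downside is that the robustness check becomes harder to pass. The crossed extreme in particular would usually fail even when the arms are equal, so it should be read as a bound and not used as a decision rule.

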A systematic review of telerehabilitation interventions [18] showed a tendency for these services to generate clinical improvements that are generally equal to those resulting from conventional rehabilitation programs. For example, efficacy of teletreatment has been demonstrated: in older populations with loss of autonomy [23], or living at home will mild to moderate dementia [24]; in individuals with mobility impairments [25]; and following total knee [26–29] or shoulder [30] arthroplasty. Interestingly, in the latest study [30], rehabilitation treatment was provided to 10 elderly patients through a videoconferencing system installed directly in their home. The intervention period length was 2 months and included supervised sessions, where a physical therapist was able to adapt exercises according to each patient’s evolution. Results of this study demonstrated that patients are able to adhere to teletreatment, and that they are able to maintain a good relationship with their physical therapists even though there was no direct physical interaction. Moreover, this remote method of receiving their rehabilitation facilitated their daily living since they were not required to travel to receive treatment. By staying home, patient motivation increased and they felt more independent in their exercises. However, an important limitation to this study was the lack of evaluation of clinical results. Therefore, although a promising avenue for rehabilitation, especially in older populations, the efficacy and functional results of telerehabilitation remain to be studied with high quality evaluations.

To our knowledge, only one study exists on telerehabilitation among patients with a proximal humerus fracture [31]. This study, realised by our research team, demonstrated the feasibility of such a service delivery to this specific population. However, our previous study was more focussed on proof-of-principle, and as such, the lack of a control group (treatment at clinic) did not permit us to affirm that clinical improvement was due to the patient’s natural recovery or to the telerehabilitation received. Thus, the main objective of the present study is to evaluate the efficacy of in-home telerehabilitation (TELE group) compared to the conventional rehabilitation in a clinic (CLINIC group) in a population with a proximal humerus fracture. Our hypothesis is that in-home telerehabilitation will prove to be a good alternative to conventional rehabilitation.

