## Methods/Design

### Study design

In our study, teletreatment will be used to provide physical therapy sessions from a service center (clinic) directly into the patients’ home. The study design is a RCT. As described in Fig. 1, there will be an evaluation at baseline (T1), 1 to 2 weeks post-fracture. Then, the 8-week intervention phase (telerehabilitation) or conventional rehabilitation in a clinic will begin at the moment prescribed by the orthopaedist, approximately 2 to 3 weeks post-fracture. Finally, a second evaluation (T2) will be held at the end of the intervention period.

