#### Costs

Economic analyses are based on the health system perspective [42]. A grid previously developed and already used to collected costs associated to teletreatment (TELE group) and conventional rehabilitation (CLINIC group) for our post-knee arthroplasty [43] will also be part of this study.

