## Discussion

This trial is the next logical step to the feasibility study conducted by our research team on 12 post-proximal humerus facture patients [31]. The previous study demonstrated that telerehabilitation seems to be a promising avenue to provide rehabilitation services to this population without adverse events. The results obtained following the present protocol will affirm the cost-efficacy of telereahabilitation treatment in an orthopaedic context, more precisely, after a proximal humerus fracture treated conservatively.

In order to control a potential selection bias, randomisation will be blind to the evaluator and participants’ characteristics will be compared pre-intervention between each group. If a group differs on some characteristics despite randomisation, corrective measures will be made in subsequent analyses. Furthermore, information bias will be controlled by using standardized measures and by calibrating all the assessors for each assessment.

This study will verify the noninferiority of in-home telerehabilitation compared to face-to-face intervention at a clinic for patients with proximal humerus fracture. In accordance with our hypothesis, we think that telerehabilitation will improve access to a rapid, less expensive, satisfactory and effective rehabilitation services.

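### Cost per point of each arm's own Constant-score change does not measure the cost-effectiveness of TELE versus CLINIC, and the differential cost that follows is undefined

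*Protocol article*

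**What the plan says.** The Statistical methods section of the protocol article gives the economic method in three sentences. The first sets the type: "Economic analysis is of cost-efficacy type". The second sets the quantity: "Cost by change-unit of the principal dependant variable (Constant score) will be determined for both groups". The third sets the comparison: "Differential cost will then be established". The section names no between-arm effect difference in connection with cost.

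Four other places bear on this:

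- **Costs:** "Economic analyses are based on the health system perspective".
- **Study design:** "there will be an evaluation at baseline (T1), 1 to 2 weeks post-fracture". T2 comes at the end of the 8-week program, so the change score spans the early healing period.
- **Abstract, Methods/Design:** cost to the public system is a listed outcome, and the groups are to be compared by t-test or chi-squared test and by a cost-effectiveness analysis.
- **Discussion:** "The results obtained following the present protocol will affirm the cost-efficacy of telereahabilitation treatment in an orthopaedic context".

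**The concern.** The question is comparative: what does TELE cost or save relative to CLINIC, and what function is gained or lost for it? A cost-per-change ratio within one arm does not answer that. Its denominator is everything that happened to the arm between T1 and T2, whether due to rehabilitation or to healing. Both arms receive the same program and there is no untreated arm, so the two parts cannot be separated within an arm.

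The authors recognise the problem in another setting. The Background says that the lack of a control group in their feasibility study "did not permit us to affirm that clinical improvement was due to the" one source or the other, natural recovery or telerehabilitation. Randomisation removes common recovery from the between-arm difference. A within-arm denominator puts it back.

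The third sentence does not settle matters. If the differential cost is the difference in mean cost, it is a sound cost comparison but is not linked to effect. If it is the difference between the two ratios, it inherits their defect. At stake is the basis for the claim that the results "will affirm the cost-efficacy of telereahabilitation treatment in an orthopaedic context".

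**Working it through.** **1. The plan's own figure.** Statistical methods gives 26 per group, SD 17, margin 10.3, one-sided alpha 0.05 and power 69%. The standard error is 17 × √(2/26) = 4.71. Power is 69.5% by the noncentral t with 50 df and 70.5% by the normal approximation. The stated 69% reproduces. It has no bearing on the ratio itself, but it is used in step 4.

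**2. The two quantities.** Let C be mean cost, E the points gained from treatment, and R the recovery common to both arms; T is TELE and C is CLINIC.

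- Per-arm ratio: C_T/(E_T + R) and C_C/(E_C + R). R stays in.
- Incremental quantity: (C_T − C_C)/(E_T − E_C). R cancels.

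**3. Illustration.** The article gives no costs, expected changes or healing share. All inputs here are assumptions, in arbitrary cost units: C_T = 800 and C_C = 1000. In case A, E_T = 2 and E_C = 12 (200 saved, 10 points lost, 20 per point). In case B, E_T = 10 and E_C = 12 (200 saved, 2 points lost, 100 per point).

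| R | Case A: TELE vs CLINIC | Case B: TELE vs CLINIC |
|---|---|---|
| 0 | 400.0 vs 83.3 | 80.0 vs 83.3 |
| 10 | 66.7 vs 45.5 | 40.0 vs 45.5 |
| 20 | 36.4 vs 31.2 | 26.7 vs 31.2 |
| 30 | 25.0 vs 23.8 | 20.0 vs 23.8 |
| 40 | 19.0 vs 19.2 | 16.0 vs 19.2 |

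In case A the ratios are equal at R = 38: 800/(2 + 38) = 20 and 1000/(12 + 38) = 20. Below that CLINIC looks better and above it TELE does, while the incremental figure stays at 20 per point. In case B the ranking does not change, but the difference between the ratios runs from −3.2 to −5.5 across the table while the incremental figure stays at 100 per point. A differential cost read as the difference between ratios would carry this dependence on R.

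**4. Which losses are compatible with noninferiority.** With t(50) = 1.676, the one-sided bound adds 1.676 × 4.71 = 7.9 points to the observed loss. The bound stays inside 10.3 only if the observed loss is below 10.3 − 7.9 = 2.4 points. Case A gives 10 + 7.9 = 17.9 and fails. Case B gives 2 + 7.9 = 9.9 and passes.

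**5. When the ratios and the costs disagree.** If TELE saves a fraction s of CLINIC's cost and loses L points against a total CLINIC change D, TELE has the lower ratio when s exceeds L/D. At the largest loss that passes (L = 2.4), the threshold is 2.4/20 = 12% for an assumed D of 20, 2.4/40 = 6% for 40, and 2.4/50 = 4.8% for 50. Above the threshold the ratios rank the arms as their costs do. Below it they favour CLINIC although TELE is cheaper.

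**The case against.** The strongest reply is that a proper comparison may already be planned. The differential cost can naturally be read as the between-arm difference in mean cost, and the Abstract plans a between-group comparison of outcomes. With noninferiority as the principal analysis, a cost difference beside it is close to what one would ask for. The Discussion's claim refers to the trial's results as a whole, not to the ratios alone. This stands as far as it goes: the third sentence is ambiguous and may be sound. But the article still names the per-arm ratio as the cost-efficacy quantity, and on neither reading does it relate the cost difference to the effect difference.

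A reader might infer something stronger: that a cheaper TELE arm losing substantial function would be declared cost-effective, or that the whole economic conclusion is uninterpretable. The documents do not support this. Under the plan's figures, losses of the size that reverse the ranking in case A would fail noninferiority, and that failure would be reported beside the ratios. Where noninferiority is met, the ratios usually rank the arms as their costs do (step 5). The healing share is also unknown, so it cannot be said that most of the change is spontaneous. The Background remark concerns an uncontrolled study and does not say that between-arm comparisons here are confounded by healing.

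It is also fair that an article leaves bootstrap details, planes and net-benefit curves to a fuller plan. Their absence is not the point. The point is the quantity the article does name.

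**Conclusion.** The concern holds in a limited form. The named ratio has the arm's whole T1 to T2 change in its denominator, so comparing ratios between arms does not measure the cost-effectiveness of TELE versus CLINIC, and the differential cost is open to two readings. The mechanism is algebraic and needs no trial data. Its size is illustrative: the reversal at 38 points rests on assumed costs and gains and on recovery being equal in both arms.

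The practical harm lies mainly in two situations. One is a trial that does not show noninferiority, which at the stated power of 69% would happen about 31% of the time even with truly equal arms. A cost-only argument then lacks support, and the ratios could be used to fill the gap. The other is a small saving, below roughly 5% to 12% of CLINIC's cost for assumed total changes of 50 down to 20 points. The primary noninferiority analysis and the sample size are untouched.

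**What to change.** Reword the economic paragraph of Statistical methods as follows:

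- Define the differential cost as the between-arm difference in mean cost, by assigned group, with a confidence interval.
- Report it jointly with the between-arm, baseline-adjusted difference in Constant score, for example as incremental net benefit over a range of values per point, or on a cost-effectiveness plane with bootstrap uncertainty.
- Do not base the cost-efficacy conclusion on a comparison of per-arm cost-per-change ratios. If they are kept, label them descriptive.
- If noninferiority is met, lead with the cost difference and its interval. If it is not, present cost and effect differences together.

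This uses the cost grid and Constant scores already being collected. It costs a little more analysis work and needs no further visits, participants or measurements.
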